# The implementation of the serial trial intervention for pain and challenging behaviour in advanced dementia patients (STA OP!): a clustered randomized controlled trial

**DOI:** 10.1186/1471-2318-11-12

**Published:** 2011-03-24

## Abstract

**Background:**

Pain (physical discomfort) and challenging behaviour are highly prevalent in nursing home residents with dementia: at any given time 45-80% of nursing home residents are in pain and up to 80% have challenging behaviour. In the USA Christine Kovach developed the serial trial intervention (STI) and established that this protocol leads to less discomfort and fewer behavioural symptoms in moderate to severe dementia patients. The present study will provide insight into the effects of implementation of the Dutch version of the STI-protocol (STA OP!) in comparison with a control intervention, not only on behavioural symptoms, but also on pain, depression, and quality of life. This article outlines the study protocol.

**Methods/Design:**

The study is a cluster randomized controlled trial in 168 older people (aged >65 years) with mild or moderate dementia living in nursing homes. The clusters, Dutch nursing homes, are randomly assigned to either the intervention condition (training and implementation of the STA OP!-protocol) or the control condition (general training focusing on challenging behaviour and pain, but without the step-wise approach). Measurements take place at baseline, after 3 months (end of the STA OP! training period) and after 6 months.

Primary outcome measures are symptoms of challenging behaviour (measured with the Cohen-Mansfield Agitation Inventory (CMAI) and the Neuropsychiatric Inventory-Nursing Home version (NPI-NH)), and pain (measure with the Dutch version of the Pain Assessment Checklist for Seniors (PACSLAC-D) and the Minimum Data Set of the Resident Assessment Instrument (MDS-RAI) pain scale). Secondary outcome measures include symptoms of depression (Cornell and MDS-RAI depression scale), Quality of Live (Qualidem), changes in prescriptions of analgesics and psychotropic drugs, and the use of non-pharmacological comfort interventions (e.g. snoezelen, reminiscence therapy).

**Discussion:**

The transfer from the American design to the Dutch design involved several changes due to the different organisation of healthcare systems. Specific strengths and limitations of the study are discussed.

**Trial registration:**

Netherlands Trial Register (NTR): NTR1967

## Background

The number of dementia patients in the Netherlands is estimated to be 235,000. Due to the aging population and the rising life expectancy, this number may exceed 500,000 in 2050. In 2000, around 30% of the people with dementia were living in nursing homes [1,2]. In nursing home residents, pain is highly prevalent: at any given time, 45-80% of the residents are in pain [3-6]. The most prominent features of pain in dementia patients are challenging behaviour, such as vocalizations (crying, screaming), noisy breathing, facial expressions (e.g. grimacing), restless or strained body expressions, aggressiveness and resistance to care [7,8]. These patterns of behaviour (like delusions, hallucinations, agitation/aggression, dysphoria/depression, anxiety, euphoria/elation, apathy/indifference, disinhibition, irritability/lability, aberrant motor behaviour, night-time disturbances, and appetite/eating disturbances) are also known as neuropsychiatric symptoms of dementia, which are a prominent feature of dementia: in nursing homes up to 80-85% of the residents have one or more of these (clinically relevant) neuropsychiatric symptoms, confusingly often also referred to as challenging behaviour [9-11].

Studies consistently show that patients with dementia are undertreated for pain [3,12-15]. Research indicates that both pharmacological interventions (analgesic medication) and non-pharmacological comfort measures are underutilized [16-18]. There are many reasons for the undertreatment of pain in this population. First, there are difficulties in the assessment of pain and challenging behaviour; the verbal communication of patients with severe dementia is often limited or completely lacking, and behavioural symptoms may provide the only indications for pain, affective discomfort or unmet needs. Second, agitated behaviour in dementia patients may point to pain [19], but it can also be related to affective discomfort. This agitated behaviour is often treated with psychotropic drugs (antipsychotic or anxiolytic medication) with several adverse effects, like drowsiness, depressed mood and falls [20].

A clinical protocol, the STI - Serial Trial Intervention (first referred to as: Assessment and treatment of Discomfort in Dementia or ADD-protocol) - was developed in the United States to address the problems in assessment and management of pain and challenging behaviour in people with dementia [8,21-23]. It is based on the 'unmet need' theoretical framework, in which behaviour can be seen as a way for cognitively impaired people to express their unmet physical and affective needs [24,25]. It is a stepped care protocol, i.e. if in one step the assessment is negative, or if targeted interventions fail to decrease symptoms, one moves to the next step. The protocol is specifically designed for dementia patients with moderate to severe cognitive impairment, because in this particular group verbal communication is often impaired and healthcare professionals therefore have to rely (at least partly) on behavioural symptoms. Since it is often unclear whether these behavioural symptoms are a result of pain or affective discomfort, a systematic approach for exploring and managing the symptoms is needed.

### The STI-protocol consists of five steps

The FIRST step is to perform a physical needs assessment that focuses on probable causes of behavioural symptoms related to pain or affective discomfort. The SECOND step is to perform a needs assessment that focuses on affective needs of people with dementia. The THIRD step concerns a trial of non-pharmacological comfort interventions, and the FOURTH step a trial of analgesics. STEP FIVE refers to consultation of other health care professionals or practitioners, or a trial of psychotropic drugs (see Figure 1).

**Figure 1 F1:**
[figure not shown]
**the STI and STA OP! intervention**.

The effects of the protocol on patient outcomes and professionals' interventions have been investigated in the USA [8,21,23]. The most recent and well-designed study [23] used a double-blinded randomized design and tested the effects of the protocol in subjects with moderate to severe dementia. The researchers established a significant decrease in the number of discomfort symptoms, measured with the Discomfort Scale - Dementia of Alzheimer type (DS-DAT) [26]. The study however did not assess pain with a measure developed for pain assessment in dementia (an observational pain instrument), quality of life, and depression. Another limitation of that study was that there was insufficient blinding of the outcome measurement.

Furthermore, it is unclear if the protocol can be effectively used in other countries, with a different other long term care (LTC) organisation. The organisation, availability and level of education of staff and availability of additional resources differ across settings and countries [27]. Dutch nursing homes, for instance, are differently organized than those in the USA [27,28]: a typical Dutch nursing home accommodates 150-200 residents, has specialized psychogeriatric wards for dementia patients, the nurses have had a longer training than in the USA, trained nursing home physicians (employed by the nursing home) provide medical care, and most nursing homes have also psychologists in their staff.

Therefore, in order to evaluate the STI in this setting, some changes in the original protocol were executed. In the original protocol for example, nurses performing the physical examination, while in Dutch nursing homes this is a task of a nursing home physician. For the analysis and care planning of behavioural problems, we introduced the expertise of the psychologist. The translated and revised version of the STI has been named STA OP!

#### Research aims and hypotheses

The purpose of this study is to assess the effects of the stepped wise Dutch version of the STI (STA OP!) versus a non-stepped wise approach to pain and behavioural symptoms.

Research questions:

1. Does STA OP! affect the number of symptoms of pain or challenging behaviours in nursing home residents differently (compared to usual care)?

2. Does the use of STA OP! lead to a change in use of analgesics and psychotropic drugs?

3. Does the use of STA OP! result in a change in use of non-pharmacological comfort interventions?

4. Does the use of STA OP! lead to a change in depressive symptoms and the quality of life in advanced dementia patients?

5. Is the effect of intervention moderated by the Apolipoprotein Epsilon 4 (Apo-E4) status of the patient?

It is hypothesized that implementation of the STA OP!-protocol will lead to less pain, fewer expressions of challenging behaviour, improved mood, higher use of pain medication and a lower use of antipsychotics (resulting in a decrease in side effects) with an increased use of non-pharmacological comfort interventions. However, we will also be able to identify findings of outcomes that reverse the direction of the hypothesis.

## Methods

### Study design

The study is a cluster randomized controlled trial. The clusters, Dutch nursing homes, are randomly assigned to either the intervention condition (implementation of the STA OP!-protocol) or the control condition (general training without the step-wise approach). Measurements take place at baseline, after 3 months (at the end of the STA OP!-training period) and after 6 months.

The study is single blinded i.e. the researcher will know the condition, while the research assistants performing the measurements and the persons analysing and score the video registrations are blinded. They will also not be informed about the specific research questions and conditions.

### Procedure

#### Recruitment

Institutions and nursing homes will be recruited within the 'University Network for Organisations of Elderly care' of the VU University Medical Center (UNO-VUmc). The aim of this collaboration network is to build greater knowledge about the best multidisciplinary care for vulnerable elderly. The network provides an infrastructure in which patient care/health care innovations, education and research can take place. Cooperation between institutions and between the institutions and the university will lead to more knowledge and better care. More than half of the eighteen member institutions will participate in this study.

#### Inclusion criteria of units

The nursing homes participating in this study will be randomized in an intervention or a control condition. Nursing homes participating in this study have to meet the following criteria: at least one psychogeriatric unit willing to participate and no major organizational changes or building activities are planned or performed in the study period. Facilities are invited to participate in the study, and after approval/inclusion randomized into control or intervention.

#### Randomization

A separate number will be assigned in order of registration to every institution, nursing home and/or participating unit. When an institution is participating with multiple affiliated nursing homes and/or units, we will investigate whether there are sources of possible contamination by professionals. Contamination is possible, if a professional (e.g. nurse, physician or psychologist) is operating in various nursing homes and/or units within the institution. If so, these different affiliated nursing homes and/or units will be randomized as one. In the event that an institution with multiple affiliated nursing homes and/or unit is participating in the study and there is no contamination by professionals, these locations and/or units will be randomized as separate participants. The randomization will take place by an independent researcher using the program "Random Allocation Software", made available by the EMGO+ Institute for Health and Care Research in Amsterdam.

#### Informed consent, inclusion and exclusion criteria

Informed proxy consent will be obtained for all residents by family/caregivers. Residents will then be screened on dementia severity, behavioural problems and indications of pain.

#### Inclusion and exclusion criteria (residents) (Table 1)

**Table 1 T1:** Instruments and the different assessment points

	Instruments	When & who?	Baseline	3 months (= ca. 12-13 weeks)	6 months (= ca. 26 weeks)
*Selection criteria*	- GDS (Reisberg)	Pre selection	NHP		
	- MDS-CPS	Pre selection	NHP		
					
*Primary Outcome*	- CMAI	Incl.	Nurse	Nurse	Nurse
	- MDS-RAI pain scale	Incl.	Nurse	Nurse	Nurse
	- NPI-NH	Incl.	Nurse	Nurse	Nurse
	- PACSLAC-D	Incl.	Nurse & VIDEO	Nurse & VIDEO	Nurse
					
*Secondary Outcome*	- Qualidem	Incl.	Nurse	Nurse	Nurse
	- Cornell & MDS-DRS	Incl.	Nurse	Nurse	Nurse
	- Medication	Incl.	RA	RA	RA
	- DS-DAT	Incl.	VIDEO	VIDEO	
	- FACS	Incl.	VIDEO	VIDEO	
					
*Control variables/Demographics*	- (co-) Morbidity	Incl.	NHP		
	- Hospitalisation, fixation etc.	Incl.	RA	RA	RA
	- Demographics; sex, age, background	Incl.	RA		
	- ADL (Katz)	Incl.	Nurse		
	- Apolipoprotein E4	Incl.	RA		

NHP = Nursing Home Physician, Nurse = caregiver, RA = research assistant, Incl. = included residents

Residents to be entered into the study meet the following (ABC) pre-selection criteria:

A) Moderate to severe cognitive impairment, according to the Global Detoriation Scale (GDS) [29]. Those residents with a GDS score of 5, 6 or 7 will be eligible for this study.

B) No chronic psychiatric diagnosis other than a dementia associated diagnosis.

The GDS score and also the absence or presence of a chronic psychiatric score (see criteria 1 and 2), will be assessed by the nursing home physician.

Proxy consent will be obtained for all residents meeting these two criteria (A & B). However, residents who are to be actively enrolled in the experimental or control condition will have to meet an additional selection criterion.

C) The criterion to enter the study protocol is the amount of clinically significant symptoms of pain and/or challenging behaviour. Inclusion criteria are: a score of at least 44 on the Dutch version of the Cohen-Mansfield Agitation Inventory (CMAI) [30,31]or a score of at least 4 (frequency × severity) on items of the Neuropsychiatric Inventory - Nursing Home Version (NPI-NH) [32,33]or an indication of clinically relevant pain (intensity × frequency ≥ 2) according to the Minimum Data Set of the Resident Assessment Instrument (MDS-RAI)-pain scale [34] in measurement week 0 (baseline).

The following data will be gathered for all the included residents: Pain observation (Dutch version of the Pain Assessment Checklist for Seniors; PACSLAC-D) [35-37] Depression (Cornell and MDS-RAI depression scale) [38,39] Quality of life (Qualidem) [40-42], ADL (Katz) [43], co-morbidity, demographics and Apolipoprotein Epsilon 4 (from Buccal mucosa swabs). In addition, 5-minutes video recordings will be made for a blinded scoring of pain and/or discomfort.

This inclusion procedure will take place on units in the intervention condition, as well on units in the control condition. These control units will be instructed to treat the included residents with 'standard care'.

#### 'Clinical' inclusion of residents

Those residents who initially do not score above the threshold on the NPI-NH, MDS-RAI pain scale or the CMAI, but who have a change in behaviour after the instrument screening, can be included in the study (after contacting the researcher and after obtaining proxy informed consent). Newly admitted residents on the unit can, after a six week 'adjustment period', follow the same procedure. The resident will (again) be assessed with the same instruments as the regular residents included, after approval by the researcher. Final analysis will be performed with and without these additional groups.

### Sample size and power analysis

One of the primary outcome measures in this study is the CMAI, a behavioural observation scale with 29 behavioural items. Each item may be scored between 1 and 7, depending on the frequency of existing symptoms. The range on the CMAI is 29-203. In Dutch nursing homes the median is 44 [44]; there is no normal distribution, but the distribution of the change is more or less normally distributed. The standard deviation of difference scores (difference of 4) is 13. The expected difference is however larger (at least 10 points). To detect a 15% difference between the intervention (STA OP!-protocol) and control condition with an α = .05 and β = .80, 56 residents will be required. However, in cluster randomization, a design effect should be taken into account; clustering of items (consistency of CMAI items [ICC] among residents in a unit is .10) and also the effect of large differences in sample sizes per cluster enhances the design effect [45].

In this study the design effect was estimated at 1.5; So, 1.5 × 56 = 84 residents (after 4 weeks) will be needed in total to detect a 15% difference with an α = .05 and β = .80. However, we expect a 50% dropout due to non-response and loss to follow-up, i.e. we will need 168 patients in total; 84 in the intervention- and 84 in the control group.

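### The sample size of 56, 84 and 168 residents is the one for a 10-point CMAI difference, but the protocol attaches it to a 15% difference whose base is not stated

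*Protocol article*

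**What the plan says.** All the inputs stand in the protocol article under *Sample size and power analysis*.

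- Level of the scale: "In Dutch nursing homes the median is 44". This is a reference figure for Dutch nursing homes. No expected baseline mean for the trial's own residents is given.
- Variability: "The standard deviation of difference scores (difference of 4) is 13".
- Effect in points: "The expected difference is however larger (at least 10 points").
- Effect attached to the sample size: "To detect a 15% difference between the intervention (STA OP!-protocol) and control condition", "with an α = .05 and β = .80, 56 residents will be required".
- After multiplying by a design effect of 1.5, the section reaches 84 "residents (after 4 weeks) will be needed in total to detect a 15% difference".
- A 50% allowance for dropout then takes 84 to 168, split 84 and 84 between the arms.

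Two passages elsewhere matter. The resident inclusion criteria admit residents with "a score of at least 44 on the Dutch version of the Cohen-Mansfield Agitation Inventory (CMAI"), or with a qualifying NPI-NH item score, or with clinically relevant pain on the MDS-RAI scale. The *Study design* section gives the assessment times: "Measurements take place at baseline, after 3 months (at the end of the STA OP!-training period) and after 6 months".

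**The concern.** The section names two effect sizes, 10 points and 15%, and never says that they are the same. They are not the same on the one CMAI level it prints: 15% of 44 is 6.6 points, and 10 points is 22.7% of 44. The sample size can belong to only one of them, and the 80% power claim is made for the 15%.

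The CMAI is the only outcome used to size the trial, so this sentence is what readers will use to judge which effects the trial could be expected to detect. If the numbers were derived for a larger effect than the one named, the power claim is too favourable, by an amount that depends on the missing base.

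**Working it through.** **Inputs.** SD of change 13, difference 10 points or 15%, median 44, design effect 1.5, dropout 50%, equal arms and alpha .05, all from the sample size section. Two readings are assumed: the test is two-sided (sidedness is not stated), and the printed beta of .80 means power of .80.

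**1. Reproduce the stated figure with 10 points.** Normal approximation, per arm:

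n = 2 × (1.960 + 0.842)² × (13/10)² = 26.5, so 27 per arm, 54 in total.

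The exact two-sample t-test gives 27.5, so 28 per arm, **56 in total**. Then 56 × 1.5 = **84**, and 84 / (1 − 0.5) = **168**. All three printed numbers are matched. Power at 28 per arm for 10 points is 80.7%, and the smallest difference with 80% power is 9.9 points.

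**2. Try to reproduce it with 15% of 44.** 0.15 × 44 = 6.6 points.

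n = 2 × (1.960 + 0.842)² × (13/6.6)² = 60.9, so 61 per arm, 122 in total. The t-test gives 61.9, so 62 per arm, 124 in total.

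Other variants do not give 56 either: a one-sided test needs 96 (normal) or 98 (t-test) in total, and a paired or one-sample t-test needs 33 (two-sided) or 26 (one-sided).

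Carrying 124 through the same chain: 124 × 1.5 = 186 analysed, and 186 / 0.5 = 372 enrolled, against 168 stated.

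**3. Power that the stated numbers give for a 15% difference.** The 84 analysed residents divided by the design effect of 1.5 are 56 effective residents, 28 per arm. The standard error of the difference is 13 × √(2/28) = 3.47 points. Since the base of the 15% is not given, it is varied (two-sided t-test):

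| Assumed base | 15% in points | Power |
|---|---|---|
| 44 (printed median) | 6.6 | 46% |
| 50 | 7.5 | 56% |
| 55 | 8.25 | 65% |
| 60 | 9.0 | 72% |
| 66.1 | 9.9 | 80% |
| 66.7 | 10.0 | 81% |

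At base 44 the normal approximation gives 48% in place of 46%. Power passes 50% at 6.93 points, a base of 46.2. Only the first base is printed in the article; the others are assumptions.

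**4. Could 56 be per arm?** With 56 per arm the t-test detects 6.94 points with 80% power, which is 15.8% of 44, and power for 6.6 points is 76%. That comes close to the 15%, and 56 × 1.5 = 84 per arm would give 168. But the section says that 84 are needed in total, and it reaches 168 by allowing for 50% dropout. On the per-arm reading 168 is already used up before any dropout. If half are then lost, 84 residents remain, and power for 6.6 points is 46% again.

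**The case against.** The strongest reply is that the article never says 15% of 44. The 44 describes Dutch nursing homes in general, and it is also the CMAI entry cut-off, so everyone who enters by the CMAI route starts at or above it. A trial mean above 44 is plausible, and with a mean near 66 to 67 the points, the percentage and the sample size all agree. On this view nothing is miscalculated: 56 follows from the two preceding figures, and both later steps are correct. What is missing is one number.

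Much of this stands. The sums are right, and the fault lies in the effect attached to them. The 46% is conditional on a base of 44. A reader might infer that the trial would miss a 15% effect more often than it finds it. The article does not support that, because a base only 2.2 points above 44 brings power to 50%. Nor can one say that no reading makes the section consistent, because a base near 66 would. It also goes too far to say that a null result would be misread as excluding a 15% effect, since what a null result excludes depends on its confidence interval. Finally, the 46% describes an unadjusted two-group comparison, whereas *Statistical analyses* plans multilevel models adjusted for baseline scores.

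What does not stand is the rescue. Nothing in the article supports a mean near 66. The CMAI cut-off is one of three alternative routes, so residents who enter on NPI-NH or pain may score below 44, and the clinical inclusion route also admits residents who first scored below the thresholds. The planned adjustment plays no part in the printed calculation, which is reproduced by an unadjusted t-test with SD 13.

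**Conclusion.** The concern holds in this form: the sample size was evidently derived for a 10-point difference in CMAI change and is presented as giving 80% power for a 15% difference with no stated base. On the only CMAI level printed, the two differ: 10 points is 22.7% of 44, and 15% of 44 is 6.6 points.

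The size of the power shortfall depends on the missing base: about 46% power if it is 44, 56% to 72% for bases from 50 to 60, and 80% only near 66. These figures assume SD 13, a two-sided 5% t-test, 84 analysed residents and a design effect of 1.5.

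Two smaller slips sit in the same sentences. Read literally, a beta of .80 means 20% power; power is clearly meant. The 4-week time point matches no assessment in *Study design* or Table 1, which have baseline, 3 months and 6 months. Neither slip changes the power figures.

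**What to change.** Keep 168 and restate what it delivers, for example: *84 analysed residents (design effect 1.5) give 80% power for a 10-point difference in CMAI change (SD 13).*

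Then either delete the 15%, or state its base and the power for that difference. If the base is the median of 44, that power is about 46%. If another base was used, giving it with its source resolves the point.

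In the same edit, write power = .80 in place of beta = .80, and replace the 4-week reference by whichever of the 3- or 6-month assessments the calculation refers to.

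The cost is wording only: no extra residents and no change to allocation or analysis. The downside is that the stated detectable effect becomes less favourable.

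### Power is mislabelled as β = .80, and the sample size makes no allowance for the small, unstated number of randomised clusters

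*Protocol article*

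**What the plan says.** All the sample size figures are in the protocol article under Sample size and power analysis. On the CMAI, "The standard deviation of difference scores (difference of 4) is 13", and "The expected difference is however larger (at least 10 points"). From these the article concludes that "with an α = .05 and β = .80, 56 residents will be required". It gives an ICC of .10 among residents in a unit, notes that uneven cluster sizes raise the design effect, and continues: "In this study the design effect was estimated at 1.5; So, 1.5 × 56 = 84 residents". The target and error rates are then repeated for the clustered total: 84 "will be needed in total to detect a 15% difference with an α = .05 and β = .80". An expected 50% dropout doubles 84 to 168.

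The number of randomised clusters appears nowhere. Under Recruitment, "More than half of the eighteen member institutions will participate in this study", which implies at least 10 institutions. Under Randomization, homes or units that share staff are randomised as one, and otherwise separately. Under Statistical analyses, the planned analysis is multilevel with adjustment for baseline scores.

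**The concern.** There are two faults of different kinds.

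The first is a label. β conventionally denotes the type II error, so a β of .80 literally claims 20% power. It is written this way twice.

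The second is a missing step. In a cluster trial the arm effect is a contrast between clusters, so the uncertainty in its standard error depends on how many clusters there are, roughly K−2 degrees of freedom for K clusters in two arms. A design effect inflates the variance for correlation within clusters. It does not replace the resident-level degrees of freedom on which the 56 was computed. With few clusters, the power claimed for 84 clustered residents is then not the power of 56 individually randomised ones.

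At stake is whether the stated 80% describes the trial as randomised. A reader cannot tell, because the cluster count that decides it is not reported.

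**Working it through.** **Inputs.** From Sample size and power analysis: difference 10 points, SD of change 13, α = .05 (two-sided assumed, since this reproduces the 56), ICC .10, design effect 1.5, 84 analysed. K is not given and has to be inferred or varied.

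**1. Reproduce the plan's figure.** With 28 per arm, SE = 13 × √(2/28) = 3.474, and the noncentrality is 10/3.474 = 2.878. A two-sided t-test on 54 df has power 80.7%. With 27 per arm it is 79.2%, so 28 per arm (56 in total) is the smallest size that reaches 80%. Then 56 × 1.5 = 84 and 84/(1 − 0.5) = 168. All three figures reproduce.

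**2. What the design effect does.** For 84 residents (42 per arm) at design effect 1.5, SE = 13 × √(2 × 1.5/42) = 3.474. The SE, and so the noncentrality, is the same as before. The 80.7% carries over only if 54 df carry over as well.

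**3. Clusters implied by the plan's figures.** With equal clusters of m analysed residents, 1.5 = 1 + (m − 1) × .10 gives m = 6 and K = 84/6 = 14. With unequal sizes, design effect = 1 + ((1 + CV²)m − 1) × ICC, so m(1 + CV²) = 6 and K = 14(1 + CV²). The article gives no CV. A CV of 0.7 would give about 21 clusters and a CV of 1 would give 28.

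**4. Power for 10 points on K−2 df, design effect held at 1.5** (noncentrality 2.878):

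| K | df | Power | Difference detectable with 80% power |
|---|---|---|---|
| 10 | 8 | 71.3% | 11.1 |
| 14 | 12 | 75.3% | 10.6 |
| 21 | 19 | 77.9% | 10.3 |
| 28 | 26 | 79.1% | 10.1 |
| 39 | 37 | 80.0% | 10.0 |

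At this design effect, 80% is first reached at 39 clusters.

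**5. The same, with the design effect following cluster size** (84 analysed, equal clusters, ICC .10):

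| K | m | Design effect | Power |
|---|---|---|---|
| 10 | 8.4 | 1.74 | 65.0% |
| 14 | 6 | 1.50 | 75.3% |
| 20 | 4.2 | 1.32 | 82.7% |
| 21 | 4 | 1.30 | 83.5% |
| 28 | 3 | 1.20 | 87.2% |

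The two tables agree only at 14 equal clusters. Beyond that, the first applies if uneven sizes keep the design effect at 1.5, and the second applies if sizes are equal.

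**The case against.** The strongest reply is that the stated 80% reproduces from the article's own inputs, while any shortfall needs a cluster count that the article does not give. This stands against a flat claim that the power is wrong. A reader might infer 14 to 21 clusters and a power of 75–78%. The documents do not support that range as fact: 14 assumes equal clusters of 6 analysed residents, and 21 needs an assumed CV of 0.7. The ICC is also quoted for units, whereas homes or merged groups may be what is randomised. If 6 per cluster was meant before dropout, there would be 28 clusters. The reply does not rescue the step itself, because the 80% that reproduces belongs to an individually randomised trial of 56.

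Second, the planned baseline adjustment could recover the loss. With equal variances at baseline and follow-up and correlation ρ, adjustment multiplies the variance of a change-score analysis by (1 + ρ)/2. At ρ = .7 the factor is .85, and power on K−2 df is about 82% at 14 clusters and 84% at 21. The article gives no ρ, so this is illustrative, but it shows that the shortfall is not certain. The expected difference is also put at 10 points or more; at 10.5 points power would be 79% and 82% respectively.

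Third, a reader might conclude that the type I error exceeds .05. Against a normal reference, 2 × P(t > 1.96) is 7.4% on 12 df and 6.5% on 19 df. The article does not say that a normal reference will be used, and the choice of df method belongs to an analysis plan that is not shown. These figures are only a conditional remark, and an approximate one: a simulation of 14 clusters of 6 gave 6.4%.

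Fourth, a reader might take the label literally, since 20% power with 56 residents corresponds to 3.94 points, close to the 4 points named in the same paragraph. That reading is strained. The article sets 4 points aside for a larger expected difference, and 56 is exactly the 80% size at 10 points.

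**Conclusion.** The point holds as a minor one. The β label is wrong and changes no number. The calculation carries a resident-level t-test into a cluster trial by a design effect alone, with no allowance for few clusters.

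If the ICC of .10 and the design effect of 1.5 describe the 84 analysed residents in equal clusters, power for 10 points is about 75% rather than 80%. With the design effect held at 1.5, the range is about 71% to 79% over 10 to 28 clusters. If clusters are equal and smaller than 6, the design effect falls and power can exceed 80%; if they are larger, it rises and power is lower still. All of this ignores any gain from baseline adjustment.

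It also takes 10 points as the target because that reproduces the 56. The article also names a 15% difference, and 15% of the median of 44 is 6.6 points. That mismatch is a separate matter, which this correction does not settle.

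**What to change.** Replace β = .80 with power (1−β) = .80 in both places. State the number of randomised clusters after homes and units that share staff have been merged, and the expected number of analysed residents per cluster. Recompute the design effect from those figures, including any allowance for uneven sizes, and restate either the power for 10 points or the difference detectable with 80% power, using K−2 df. With 14 equal clusters of 6 this would read about 75%, or 10.6 points. If credit is taken for baseline adjustment, give the assumed correlation. The reference distribution for the arm effect can be left to the analysis plan, provided that it matches the restated calculation.

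The cost is a few lines of wording and possibly a stated power some points lower. Enrolment stays at 168.
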